### 3.2 Criteria for discontinuing interventions

The project leader is promptly notified (within 24 hours) if immediate safety and protective measures have to be taken during the conduct of the research project. The Ethics Committee will be notified of these measures and of the circumstances necessitating them within 7 days. If a serious event occurs, the research project will be interrupted and the Ethics Committee notified on the circumstances within 7 days according to Ordinance on Human Research (HRO) Art. 21.

A serious event is defined as any adverse event where it cannot be excluded, that the event is attributable to collection of health-related personal data, and which:

requires inpatient treatment not envisaged in the protocol or extends a current hospital stay;results in permanent or significant incapacity or disability; oris life-threatening or results in death

It is important to note that since the study is purely observational, treatment related complications or morality does not fall under these regulations. Severe adverse events in the setting of this study were defined as any events related to the data collection and processing such as violations of confidentiality or others.

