### 2.2 Eligibility criteria

#### Inclusion criteria

All patients aged ≥ 18 years undergoing any left sided emergency or elective colorectal resections for any indication with or without primary anastomosis in one of the nine participating hospitals are eligible to be part of the study population. Patients should have given or will give a general consent for the use of their data for research purposes. As this is a quality improvement project and the modified standard according to the CB is rolled out over the entire treating institution, patients cannot opt for non-treatment according to the CB but may deny data usage and acquisition within the trial by denying general consent.

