## 3. Interventions

### 3.1 Intervention description

During the control period, patients are treated according to their local standard of the contributing hospitals. During this period no special interventions are planned, but baseline data will be obtained. Data according to the CRF will be collected for the pre-, intra-, and postoperative course, including all complications according to the Clavien Dindo Classification [28] for each complication to calculate the primary outcome measure (CCI) [27].

After the control period the full CB is implemented during a period of 1 month in every contributing hospital.

The CB will consist of the following items:

Preoperative optimization of the nutritional status: Perform Nutritional Risk Score (NRS), measure albumin or prealbumin preoperatively and initiate nutritional support and delay surgery by at least two weeks if clinically feasible to allow improvement of nutritional status in case the NRS is >2.Preoperative showering with an antiseptic agent on the night before or the day of admission for all patients.Antibiotic decontamination (which is optional according to institutional preference) and mechanical bowel preparation (for all).Administer preoperative antibiotic prophylaxis within 60 minutes prior to skin incision (not after and not any earlier).Hair removal in the operative field with clippers (no shaving).Peri-, intra-, and postoperative warming to maintain body temperature above 36 °C and peri-, intra- and postoperative glucose control below 9 mmol/l until patient leaves the wake-up area.Usage of a wound protection device (such as Alexis® wound protector or others).Change of gloves and instruments after anastomosis respectively the contaminated phase in patients with end colostomy formation.Anastomosis only with experienced senior surgeon present in the operating theatre for any elective and emergency procedures (senior surgeon will be defined as follows: “Schwerpunkt Träger Viszeralchirurgie” and/or “European Board of Surgical Qualification (EBSQ) Colorectal”, and/or certified operator according to Deutsche Krebs Gesellschaft (DKG) alternatively a head of department/local principal investigator can name surgeons in case of other qualification if deemed necessary).

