### 3.3 Strategies to improve adherence to interventions

Compliance to the beforehand declared local standards are monitored by chart reviews. Patients will be contacted for quality control measures 30 days after surgery to detect any post discharge complications and allow possibly necessary readmissions or outpatient controls. Adherence to the CB is monitored by checklists and overviewed by the responsible study physicians. In case of non-adherence to the protocol individual feedback is given to the responsible surgeon. The number of patients, who discontinue the interventions implemented in the colorectal bundle will be collected for every network hospital separately.

In worst case patients in centres will be excluded in case of excessive non-adherence due to possible contamination of the data pool. For this case the data collection period will be extended until full compliance to the CB is achieved for a period of at least 6 months.

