### 3.4 Relevant concomitant care permitted or prohibited during the trial

For the subgroup of patients receiving antibiotic decontamination active bacterial infection requiring systemic antibiotics or patients that received IV or oral antibiotics in the past 7 days prior to the planned decontamination will lead to exclusion of this component in these particular patients. Other circumstances that lead to exclusion from antibiotic decontamination are terminal kidney disease or the impossibility to take antibiotic decontamination medication (e.g., vomiting, dysphagia) at time of screening, pregnancy or breastfeeding, emergency or expedited surgery.

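### Sections 3.7 and 4.3 give conflicting analyses for the secondary endpoints, and the one-sided test in 4.3, read in the direction of H1, cannot declare an increase in deaths or leaks

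*Protocol article*

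**What the plan says.** Section 1.1 lists among the secondary objectives the impact of the colorectal bundle (CB) on mortality and on anastomotic leak rates. Section 3.5 makes both 30-day secondary endpoints.

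Two places then say how secondary endpoints are analysed:

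- Section 3.7, last sentence: by descriptive statistics.
- Section 4.3: primary and secondary outcomes are analysed with a one-sided Fisher's exact test, with p < 0.05 taken as significant. The H0 and H1 printed just above it concern the average Comprehensive Complication Index only. H1 is that the average is lower after the bundle.

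On safety, section 3.2 defines a serious event as "any adverse event where it cannot be excluded, that the event is attributable to collection of health-related personal data" and adds that "since the study is purely observational, treatment related complications or morality does not fall under these regulations". The same section opens with a 24-hour notice to the project leader "if immediate safety and protective measures have to be taken during the conduct of the research project". Section 3.1 says "After the control period the full CB is implemented during a period of 1 month in every contributing hospital", and the inclusion criteria say that "patients cannot opt for non-treatment according to the CB".

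**The concern.** A statistician working from this document cannot tell whether mortality and leakage will be tested. The choice matters because the one test named looks in one direction. The objective asks what the bundle does to deaths and leaks, and that includes making them worse. A one-sided test for a reduction returns a p-value near 1 when events rise, and the report would then read only that no reduction was shown. The excess would be visible in the counts, but nothing in section 4.3 would say how large an increase the data support or leave open.

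The wording of section 3.2 adds a smaller difficulty. The study brings in the bundle and follows up departures from it (section 3.3: "In case of non-adherence to the protocol individual feedback is given to the responsible surgeon"), so calling it purely observational is an awkward reason for leaving treatment-related events outside the rules. A site could take the sentence to mean that the opening 24-hour clause does not apply to protective measures prompted by a bundle item.

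**Working it through.** The plan gives no figure for this point, so there is none to reproduce. The conflict itself is textual: section 3.7 has description and no test; section 4.3 has a test, with a level and one side. Both cover the same endpoints.

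The arithmetic below only illustrates what the one-sided test would do with an increase.

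**Inputs**

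- 149 patients per arm, 298 in total (section 3.7).
- Leak rates of 1.5 to 22% at institutional level (section 1). The value of 10% is assumed, as a point inside that range.
- A doubling under the bundle: assumed.
- Mortality: the document gives no rate; 1%, 3% and 5% are assumed.
- All patients have an anastomosis, or 70% do (assumed): 149 x 0.7 = 104 per arm.
- Direction of the one-sided test: reduction under the bundle, taken from H1.

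**Formulas**

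- One-sided Fisher p = P(X ≤ x), where x is the number of events under CB and X is hypergeometric with the total number of events fixed.
- Difference d = p1 − p0 (CB minus control). Wilson limits (l, u) for each arm, then Newcombe: lower = d − √[(p1 − l1)² + (u0 − p0)²]; upper = d + √[(u1 − p1)² + (p0 − l0)²].

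**Leading case, 15 versus 30 leaks**

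- Control: 15/149 = 0.1007, Wilson 0.0620 to 0.1595. CB: 30/149 = 0.2013, Wilson 0.1448 to 0.2729. d = 0.1007.
- Lower = 0.1007 − √(0.0565² + 0.0588²) = 0.1007 − 0.0815 = 0.019.
- Upper = 0.1007 + √(0.0715² + 0.0387²) = 0.1007 + 0.0813 = 0.182.
- One-sided p = 0.995; two-sided p = 0.023.

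**All cases**

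| Endpoint, assumed control rate | n per arm | Control vs CB | One-sided p | Two-sided p | Difference, points (95% CI) |
|---|---|---|---|---|---|
| Leak 1.5% | 149 | 2 vs 4 | 0.89 | 0.68 | +1.3 (−2.4 to +5.5) |
| Leak 10% | 149 | 15 vs 30 | 0.995 | 0.023 | +10.1 (+1.9 to +18.2) |
| Leak 22% | 149 | 33 vs 66 | >0.999 | <0.001 | +22.1 (+11.5 to +32.1) |
| Leak 10%, 70% anastomosed | 104 | 10 vs 21 | 0.99 | 0.050 | +10.6 (+0.8 to +20.3) |
| Leak 10%, no change | 149 | 15 vs 15 | 0.58 | 1.00 | 0.0 (−7.0 to +7.0) |
| Death 1% | 149 | 1 vs 2 | 0.88 | 1.00 | +0.7 (−2.5 to +4.1) |
| Death 3% | 149 | 4 vs 8 | 0.93 | 0.38 | +2.7 (−2.1 to +7.8) |
| Death 5% | 149 | 7 vs 14 | 0.97 | 0.17 | +4.7 (−1.3 to +10.9) |

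In the one-sided column, the no-change row and the doubling rows all read as no reduction shown. The interval tells them apart where the data allow it. With 104 per arm the two-sided Fisher p is 0.0502, just above 0.05, while the Newcombe interval excludes zero, so that case is borderline.

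**The case against.** Section 4.3 states no direction for the secondary outcomes; reading it from H1 is an inference, and H1 is about the index alone. That stands, so the statement about an undetectable increase is conditional. The conflict between the two sections does not depend on it.

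The conflict covers every secondary endpoint, not deaths and leaks alone. Interval format is often left to the analysis plan, and descriptive reporting does not rule intervals out. This too is fair. The proposal is in effect section 3.7's approach with intervals named, and what makes it a finding is that section 4.3 contradicts it.

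The illustration assumes every doubling, pools over centres despite the wide institutional spread, and is not adjusted for confounding between periods. The analysed number may also exceed 149 per arm, since all eligible patients over six months are screened. It therefore shows how the test behaves and forecasts nothing.

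A reader might infer something stronger from section 3.2: that bundle-related harm goes unrecorded or unprotected, or that the study is wrongly classified under the Ordinance on Human Research. The document does not support this. The limit to data-collection events comes from the definition given under Art. 21, not from the sentence about observation. The opening 24-hour clause is not restricted by cause, and section 6.1 exempts urgent protective measures from prior approval. Complications and deaths are collected to day 30 and enter the primary endpoint. The inclusion criteria frame the roll-out as quality improvement, and an ethics committee approved the study. Whether the regulatory category is right cannot be judged from this article.

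**Conclusion.** The protocol contradicts itself on the analysis of its secondary endpoints, and this needs correcting as written. If the one-sided test follows H1, it cannot declare an increase in 30-day mortality or leakage, although the impact on both is a stated objective.

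The practical size depends on the event rate. For leakage near 10%, a doubling at the planned size would show in a two-sided interval and be missed by the one-sided test. At 1.5% leakage, and for deaths at 1 to 5%, no test at this size would detect a doubling, and the gain is only that the interval states what harm remains possible. These results rest on the assumed rates, the assumed doubling and unadjusted pooled counts.

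The phrase in section 3.2 is a minor wording fault and does not amount to a safety defect.

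**What to change.** Replace the sentence on secondary endpoints in section 3.7 and the secondary part of the test sentence in section 4.3 with one statement. Secondary endpoints are described; 30-day mortality and anastomotic leakage (leakage among patients with an anastomosis) are reported as counts and as CB-minus-control differences with two-sided 95% confidence intervals. Delete the one-sided Fisher's exact test for secondary outcomes. This needs no further patients, visits or data. What is given up is a one-sided claim of reduction on these endpoints.

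Minor: in section 3.2, replace the reason based on observation with a plain statement that the Art. 21 serious-event rule covers data-collection events only, and that the opening 24-hour clause also applies to protective measures prompted by a bundle item. Do not add event review in the bundle period alone: closer scrutiny in one period could raise the complications found there and bias the before-after comparison of the primary endpoint.

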### 3.3 Strategies to improve adherence to interventions

Compliance to the beforehand declared local standards are monitored by chart reviews. Patients will be contacted for quality control measures 30 days after surgery to detect any post discharge complications and allow possibly necessary readmissions or outpatient controls. Adherence to the CB is monitored by checklists and overviewed by the responsible study physicians. In case of non-adherence to the protocol individual feedback is given to the responsible surgeon. The number of patients, who discontinue the interventions implemented in the colorectal bundle will be collected for every network hospital separately.

In worst case patients in centres will be excluded in case of excessive non-adherence due to possible contamination of the data pool. For this case the data collection period will be extended until full compliance to the CB is achieved for a period of at least 6 months.

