**Methods::**

The study will be performed among nine contributing hospitals in the extended north-western part of Switzerland. In the 6-month lasting control period the patients will be treated according to the local standard of each contributing hospital. After a short implementation phase all patients will be treated according to the CB for another 6 months. Afterwards complication rates before and after the implementation of the CB will be compared.

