### 4.3 Statistical methods

The primary objective of the study is to be measured by the CCI 30 days post-operative compared to the CCI under standard care as the control group. The average CCI of patients treated in participating hospitals before implementation of the CB will be compared with the average CCI after implementation.

We hypothesize that the CB will be effective in reducing CCI scores 30 days post-operation as compared to standard care.

H0: The average CCI of patients treated after implementation of the CB is the same as (or higher than) the average CCI before implementation.H1: The average CCI of patients treated after implementation of the CB is lower than the average CCI before implementation.

The analysis of the primary and secondary outcomes will be made based on a one-sided Fisher`s Exact Test with the assumption of an alpha level of p < 0.05 to be considered significant. A multivariable analysis will be performed to control for the above-mentioned confounding factors concerning the primary endpoint.

For adjusted analyses, the following potential confounding factors are accounted:

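### The adherence-based exclusion and extension rule in section 3.3 has no control-period counterpart, conflicts with the primary before-after comparison, and could bias it

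*Protocol article*

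**What the plan says.** All of this is in the protocol article.

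- **Exclusion (3.3):** "In worst case patients in centres will be excluded in case of excessive non-adherence due to possible contamination of the data pool".
- **Extension (3.3):** in that case "the data collection period will be extended until full compliance to the CB is achieved for a period of at least 6 months".
- **How adherence is measured (3.3):** "Adherence to the CB is monitored by checklists and overviewed by the responsible study physicians". For the control period, "Compliance to the beforehand declared local standards are monitored by chart reviews", but neither exclusion nor extension is attached to that monitoring.
- **Primary comparison (4.3):** "The average CCI of patients treated in participating hospitals before implementation of the CB will be compared with the average CCI after implementation". The null and alternative hypotheses use the same two groups, without an adherence condition.
- **Length of the CB period (Abstract, Methods):** "After a short implementation phase all patients will be treated according to the CB for another 6 months". Section 3.1 and the Discussion (section 7) also give 6 months.
- **Eligibility (2.2):** patients "undergoing any left sided emergency or elective colorectal resections for any indication with or without primary anastomosis". The exclusion criteria concern consent, vulnerability and recent earlier surgery. Non-adherence is not among them.

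**The concern.** Whether a patient or centre adhered to the bundle is known only after implementation, so it is a post-intervention variable. It is plausibly tied to prognosis. For example, one item asks the team to "delay surgery by at least two weeks if clinically feasible to allow improvement of nutritional status", so what is done depends on the patient's condition. It is also plausibly tied to how well a centre is run. If patients who adhered poorly leave the CB period while the control period stays whole, the two periods no longer sample the same population. A lower mean CCI after implementation could then arise partly from who was kept.

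The extension adds a second asymmetry: the CB period would run later and longer than the control period, with more exposure to any time trend. In an uncontrolled before-after design the analysis has little else to protect it against either problem.

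**Working it through.** **1. The passages side by side.** Section 4.3 compares patients treated before with patients treated after implementation. The Abstract, section 3.1 and the Discussion give 6 months for the CB period. Section 2.2 does not exclude for non-adherence. Section 3.3 allows departures from all three. The article names no analysis set that would keep the excluded patients, so the rule, if invoked, acts on the primary comparison.

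**2. Size of the crude shift.** The plan attaches no figure to the rule, so there is none to reproduce. Let q be the share of CB-period patients removed, and D the mean CCI of those removed minus that of those kept. With no bundle effect:

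mean before removal = (mean of those kept) + q × D, so bias (CB minus control) = −q × D.

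Neither q nor D is in the document; both are assumed.

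| q | D | Bias in CCI points |
|---|---|---|
| any | 0 | 0 |
| 10% | 10 | −1.0 |
| 20% | 10 | −2.0 |

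The hypothesised effect (section 1.1) is a reduction of 10 points.

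**3. Effect on the error rate.** Inputs from section 3.7: SD 12.5, one-sided 2.5% test, 149 patients per arm, variance inflation factor (VIF) 3.3.

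- SE without inflation = 12.5 × √(2/149) = 1.45.
- SE with inflation = 1.45 × √3.3 = 2.63.
- False-positive rate = Φ(q × D / SE − 1.96).

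| Shift | No inflation | VIF 3.3 |
|---|---|---|
| 0 | 2.5% | 2.5% |
| 1 point | 10.2% | 5.7% |
| 2 points | 28.1% | 11.5% |

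The VIF column belongs to an adjusted analysis, so its shift has to be read as whatever bias adjustment leaves behind.

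**4. Partial selection through urgency.** Assume 20% emergencies, adherence of 30% in emergencies and 90% in electives, and a 10-point CCI gap. Share kept = 0.2 × 0.3 + 0.8 × 0.9 = 0.78. Emergency share among those kept = 0.06 / 0.78 = 7.7%. Crude shift = (0.077 − 0.20) × 10 = −1.2 points.

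**5. A whole centre dropped from the CB period only.** Under the section 3.7 weights a middle-sized centre supplies one tenth of an arm. Assume it lies one between-centre SD (20 points) above the overall mean. Crude shift = −(0.1 × 20) / 0.9 = −2.2 points. A centre effect in the model would take up most of a constant level difference like this one.

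**The case against.** The strongest reply is that the rule is a worst-case contingency about centres. Read with the extension, it may mean that a centre's failed implementation window is replaced by a later one. That window would again contain emergency and elective patients, so individual high-risk patients would not be filtered out. If a centre left both periods, the within-centre contrast would not be biased in the way described. This stands as a fair reading, but the text does not settle whether single patients, a centre's CB period or a centre's whole data are meant. Even replacement leaves the CB period selected on compliance, and later than planned.

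Second, urgency, comorbidities, nutritional status and field contamination are listed confounders (4.3), and centre is a random effect (3.7). This stands for the measured part. It does not cover unmeasured reasons for non-adherence.

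Third, a condensed article may leave the thresholds for excessive non-adherence and full compliance to the full protocol or SAP. That is accepted, and their absence is not part of this point.

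A reader might also infer that emergency patients would be the ones removed and that full compliance could never be reached. The document does not support this:

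- The antiseptic shower may be taken on the day of admission.
- Nutritional delay applies only where feasible.
- Decontamination is optional, and section 3.4 drops that component for emergencies, not the patient.
- Table 1b schedules consent and data recording, not treatment.

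Only mechanical bowel preparation is stated for everyone without allowance for urgency, which is too little to carry that inference.

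**Conclusion.** The concern holds in this form: section 3.3 contains a one-sided, adherence-based exclusion and extension rule that conflicts with sections 2.2, 3.1 and 4.3, and applying it to the CB period only could bias the primary comparison. The likely direction favours the bundle, but the document does not prove this. It requires non-adherent patients or centres to have worse outcomes.

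The size cannot be derived from the document. With q of 10 to 20% and D of 10 (assumed), the crude shift is 1 to 2 points against a 10-point hypothesis. It is zero if non-adherence is not prognostic, and smaller after adjustment.

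Two stronger readings should not be drawn:

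- **A shift of 4 points, or 40% of the target effect** (0.2 × 20). This needs every emergency patient to be removed from the CB period and none from the control period, with assumed values for both inputs. Section 3.3 does not say that, and urgency is an adjustment variable.
- **Data collection steered by outcome results.** Section 3.3 ties the extension to compliance with the bundle, not to CCI or any interim result.

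**What to change.** - Define the primary analysis set as every eligible consented patient operated on in each centre's fixed 6-month control window and fixed 6-month CB window, regardless of adherence.
- Remove the exclusion and extension rule from the primary analysis, and reconcile section 3.3 with the Abstract and sections 2.2, 3.1, 4.3 and 7.
- Report any adherence-restricted analysis only as a sensitivity analysis with a prespecified threshold. A centre left out there should be left out of both periods.

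With q = 0 this selection bias disappears and the error rate stays at its nominal level, as far as this issue goes. The change is to wording only and needs no extra patients. The caseloads in section 2.1 sum to 350 + 120 + 200 + 85 + 270 + 100 + 85 + 80 + 125 = 1,415 a year, or about 707 in 6 months before any loss for missing consent, against 149 required per arm. The small downside is that the estimate reflects adherence as it actually occurs and may be somewhat diluted.
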